### Analysis plan

Overall study efficacy will be established using the intention-to-treat principle, in which patients are analyzed in the treatment group to which they are assigned at randomization. Length of stay may be considered a time to event time end-point with discharge as the outcome. The graphical presentation of these survival distributions for heparin and placebo groups will be estimated using the Kaplan-Meier method, and the test statistic for comparison between these two survival distributions will be based on the Log-rank test [32].

MOD score data correspond to the case of longitudinal data with correlated measurements, and as such require special statistical methods to account for the correlation among observations. To analyze this kind of clustered data, it is necessary to model both the regression of *Y *(the outcome measure) on *x *(the intervention) and the within-cluster dependence in a unified manner with the application of a random-effects model for longitudinal data [36].

For secondary outcomes, the comparisons will be presented as absolute and relative differences in 28-day mortality rates with exact 95% confidence intervals. The statistic to test this secondary null hypothesis will be the Chi-square test. Although the expectation is that randomization assists in balancing known and unknown prognostic factors, this assignment process is not a guarantee against the possibility that estimates of treatment effect will be modified by covariate imbalance. Accordingly, the estimated relative risk of mortality for heparin vs. placebo will be adjusted by the most important prognostic factors (age, APACHE II score and MOD score at baseline), using a multiple logistic regression model.

The natural heterogeneity of sepsis supports the importance of exploring the efficacy of the intervention among different subgroups of patients, as defined by characteristics of the illness. As hypothesis-generating analysis, the following interaction terms will be incorporated into the logistic model described before:

- Treatment * Source of infection (pneumonia vs. others)

- Treatment * Site of acquisition (community vs. hospital)

- Treatment * APACHE II score at baseline (continuous variable)

- Treatment * MOD score at baseline (continuous variable)

- Treatment * D-dimer at baseline (continuous variable)

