### Sample size

Length of stay may be considered a time to event end-point, with patient discharge alive as the outcome. Those who die during the hospital stay will be considered as competing risks for this analysis because they are not censored observations. With a median length of stay of 11 days, a type I error of 0.05 and a type II error of 0.2, the estimated number of patients required to detect a relative hazard of being discharged alive of 1.3 is 231 [32]. This number of events may be achieved with a total sample size of 310 patients, assuming an overall hospital mortality of 25%.

MOD score data correspond to the case of longitudinal data with correlated measurements, and as such require special considerations for calculation of power and sample size [33]. The table 3 shows different estimates of power under different assumptions of correlation among repeated observations (ρ) and differences in rate of change (Δ) with a fixed sample size of 310 participants. This sample size also will have an 80% power to detect a 50% relative reduction in the secondary outcome of overall 28-day mortality.

**Table 3 T3:** Power estimates for differences (Δ) in MOD score with a fixed sample size of 155 patients per group and selected values of correlation (ρ)

ρ Δ	3 points	2 points	1 point
0.8	100%	99%	98%
0.5	100%	98%	97%

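### The length-of-stay analysis specifies Kaplan-Meier and log-rank on discharge without saying how deaths are coded, although the sample-size section makes deaths uncensored competing events

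*Protocol article*

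**What the plan says.** Hospital length of stay is one of two primary outcomes (Protocol article, Abstract and Background). Two sections describe its analysis.

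- **Sample size:** "Length of stay may be considered a time to event end-point, with patient discharge alive as the outcome". On in-hospital deaths: "Those who die during the hospital stay will be considered as competing risks for this analysis because they are not censored observations". The section then assumes 25% hospital mortality to get from 231 events to 310 patients.
- **Analysis plan:** "Length of stay may be considered a time to event time end-point with discharge as the outcome". For the curves and the comparison of arms, this section specifies: "estimated using the Kaplan-Meier method, and the test statistic for comparison between these two survival distributions will be based on the Log-rank test".

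The Analysis plan omits the word alive, gives no coding for patients who die in hospital, and names neither a cumulative incidence function nor a competing-risk test.

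**The concern.** In ordinary use, Kaplan-Meier and the log-rank test recognise two statuses, event or censored. A patient who dies in hospital must be given one of them.

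- **Deaths censored.** This is what the Sample size section rules out. The curve treats the dead as if they could still go home, so 1 minus Kaplan-Meier does not estimate the proportion discharged alive. The log-rank test then compares only the rate of discharge among patients still alive in hospital. An effect on stay that works through mortality is outside it.
- **Deaths counted as discharges.** This contradicts discharge alive. An arm with more early deaths would appear to leave hospital sooner.

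The two codings can give different primary results. If the coding is settled after the data are seen by arm, the primary test is open to choice.

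**Working it through.** **Inputs from the Sample size section.** Median stay 11 days, hospital mortality 25%, relative hazard of discharge alive 1.3, 231 events, 310 patients (155 per arm).

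**The plan's own arithmetic.** 231 / (1 − 0.25) = 308, close to the stated 310; conversely 310 × 0.75 = 232.5 discharges alive and 310 × 0.25 = 77.5 deaths. So the sample size does not count deaths as events; if it did, all 310 patients would contribute one. (Whether 231 is the right total for a relative hazard of 1.3 is a separate question. Freedman's formula, two-sided 0.05 and 80% power, gives (1.960 + 0.842)² × (2.3/0.3)² ≈ 461, rounded up to 462 in total or 231 per arm. Nothing below depends on it.)

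**Assumptions not in the documents.** Constant hazards, 11 days as the median to any exit, no censoring other than by the coding of deaths. Total exit hazard λ = ln 2 / 11 = 0.0630 per day; discharge alive 0.75λ = 0.0473; death 0.25λ = 0.0158.

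**Formulas**
- Proportion discharged alive by t (cumulative incidence): 0.75 × (1 − exp(−λt))
- 1 − KM, deaths censored: 1 − exp(−0.75λt)
- 1 − KM, deaths counted as discharges: 1 − exp(−λt)

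| | Cumulative incidence | 1 − KM, deaths censored | 1 − KM, deaths as discharges |
|---|---|---|---|
| Day 28 | 0.622 | 0.734 | 0.829 |
| Day 60 | 0.733 | 0.941 | 0.977 |
| Median (days) | 17.4 | 14.7 | 11.0 |

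**Range.**
- With the 21% mortality that the Population section reports for an earlier cohort, day 28 gives 0.79 × 0.829 = 65% against 1 − exp(−0.79 × 0.0630 × 28) = 75%, a gap of about 10 points instead of 11.
- If 11 days is instead the Kaplan-Meier median with deaths censored, the discharge hazard is 0.0630 and the total 0.0630/0.75 = 0.0840. Day 28 then gives 0.75 × (1 − exp(−0.0840 × 28)) = 68% against 83%, a gap of 15 points.

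**Effect on the test.** Simulation under the main assumptions, 155 per arm, 4,000 runs; percentage of runs significantly favouring heparin at two-sided 0.05:

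| Scenario | Deaths censored | Deaths as discharges | Deaths kept in risk set (subdistribution) |
|---|---|---|---|
| Discharge hazard equal, death hazard doubled | 2.9% | 50% | 0% |
| Discharge hazard equal, death hazard halved | 2.3% | 0.1% | 39% |
| Discharge hazard ratio 1.3, death hazard equal | 53% | 44% | 32% |

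With no effect at all, each test rejects in about 5% of runs, both directions together. In the doubled-death scenario the hazard of any exit rises by (0.75 + 0.50)/1.00 = 1.25, close to the design target of 1.3, while the final proportion discharged alive falls from 75% to 0.75/1.25 = 60%. In the halved-death scenario it rises to 0.75/0.875 = 86%.

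**The case against.** Four points on the other side carry weight.

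1. **A third coding exists.** If patients who die stay in the risk set as never discharged, to the longest follow-up, and there is no other censoring, 1 minus Kaplan-Meier equals the cumulative incidence and the log-rank test becomes a subdistribution comparison. That would fit the Sample size section. The article does not say this is intended, so the gap remains, but a reader who infers that a quarter of patients will definitely be mishandled goes further than the text. The 25% is also a planning figure.
2. **A log-rank test censoring deaths is valid for its own question.** It tests the cause-specific hazard of discharge alive, holds its type I error, and can address a relative hazard of 1.3 for discharge alive. Where only mortality changes, a ratio of 1.0 is the right answer to that question. This stands; the limit is in what the test covers. Mortality is also compared separately, at 28 days.
3. **Counting deaths as discharges is the least plausible reading.** It conflicts with both the definition and the event arithmetic in the Sample size section. That harm will be scored as benefit is therefore a risk of leaving the coding unstated, not something the plan prescribes.
4. **An article condenses.** Detail may sit in a fuller document. But here the article makes two statements that do not fit together, which is more than an omission.

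Two stronger inferences are not supported. The claimed 80% power for a 50% relative reduction in 28-day mortality does not forecast such a reduction, so one cannot conclude that deaths will be unbalanced between arms. Nor can one conclude that deaths are mishandled in the Multiple Organ Dysfunction score analysis: the text names only the "application of a random-effects model for longitudinal data", and handling of scores after death may properly be left to the full plan.

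**Conclusion.** The concern holds as an inconsistency in the stated analysis of a primary endpoint. Each ordinary coding of deaths under the named methods conflicts with the Sample size section, and the one coding that would agree with it is not stated. The fault is clearest for the curves: under the stated assumptions Kaplan-Meier overstates the day-28 proportion discharged alive by about 11 points if deaths are censored and about 21 points if they count as discharges. For the test, the fault is that the estimand is undeclared: it could be the cause-specific hazard of discharge alive, the subdistribution hazard or the hazard of any exit, and these respond differently to a change in mortality. The sizes rest on constant hazards and on the reading of the 11-day median; the inconsistency does not.

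**What to change.** In the Analysis plan:

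- Restore discharge alive as the event and state that in-hospital death is a competing event.
- Replace the Kaplan-Meier curves with cumulative incidence (Aalen-Johansen) curves, by arm, for discharge alive and for death.
- Declare one matching primary test and effect estimate with 95% confidence interval: either Gray's test with a subdistribution hazard ratio, or a cause-specific log-rank test and hazard ratio. Statisticians may reasonably differ on which. The simulation shows the trade: the cause-specific test is stronger when only discharge is affected (53% against 32%), the subdistribution test when only mortality is (39% against 2.3%).
- Whichever is primary, report cause-specific hazard ratios for both discharge alive and death.

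Cost: rewording, standard software and slightly more complex reporting; no new data. Because the first interim analysis has already been done, the change needs a dated, documented amendment. It should be made before unblinding, by people who have not seen results by arm; the Interim monitoring section gives that access only to the data-coordinating statistician and the monitoring board.

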## Background

Sepsis is considered a leading cause of death worldwide with approximately 18 millions cases annually and a mortality rate of almost 30% [1]. In Colombia, the country in which this study will be conducted, there are no national estimates of sepsis incidence. However, our previous investigations have provided some relevant data: in a 650 bed University-based Hospital, bacteremia and/or sepsis were considered a main diagnosis in 7 out of 100 admissions to the emergency room; and blood cultures were requested in 2 out of 10 inpatients at some time during their hospitalization [2,3]. The overall 28-day sepsis mortality rate ranged from 25% to 40%, depending on the growth of microorganisms in blood cultures [2-4].

In the last two decades the accepted standard treatment for sepsis has resulted in only a slight decrease in mortality, and that decrease has been overshadowed by an almost 300% increase in incidence [5]. Unfortunately, the search for efficacious therapeutic approaches has largely failed and only a few of the recent interventions -as early goal directed therapy, activated protein C and low dose steroids- have shown success in improving survival [6,7]. However, these interventions were tested only in patients with severe sepsis and septic shock and although these groups exhibit the highest mortality, they may represent less than 50% of the total affected population [8,9]. Furthermore, these interventions necessitate special devices, tests or drugs that might be unavailable or simply unaffordable in resource-limited settings.

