### Population

An ideal therapy should be viable for septic patients at the earliest stage in their clinical course once the infectious process is suspected or confirmed, and not only at the point of admission to intensive care as has been the case for virtually all previous sepsis trials. Although the definitions for severe sepsis and septic shock have been relatively easy, the identification of that "less ill" population has been really hard to meet. In fact, currently we are lacking a standard definition for sepsis. We have shown [30] that in the setting of the proposed study, the classical systemic inflammatory response syndrome (SIRS) definition was not inclusive enough to identify the full spectrum of patients, since its sensitivity was less than 70% for a cohort with a median length of stay of 11 days and an overall hospital mortality of 21%. Thus, we are proposing a set of inclusion criteria that may be useful to include the wide spectrum of the syndrome. In addition to fulfilling the operational criteria for inclusion, we are restricting our population to the patients with a clinical picture as severe enough to require inpatient treatment.

Patients will be recruited, between July 2005 and June 2007, through the emergency room at Hospital Universitario San Vicente de Paul. This is a 650-bed University Hospital in Medellín, Colombia and is a referral center for a region with approximately 3 million habitants. Patients aged 18 years or older, males or females, hospitalized with a suspected or confirmed infection, unexplained fever, unexplained altered mental status or unexplained arterial hypotension (systolic blood pressure < 90 mm Hg or a decrease > 40 mm Hg) will be considered potentially eligible for the trial.

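### The adjusted "relative risk" of 28-day death is assigned to a logistic regression, whose treatment coefficient is a conditional odds ratio; at the mortality expected here the two are not interchangeable

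*Protocol article*

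**What the plan says.** All of this concerns the secondary outcome, 28-day all-cause mortality.

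- **Unadjusted comparison** (Analysis plan): "the comparisons will be presented as absolute and relative differences in 28-day mortality rates with exact 95% confidence intervals". The test is a chi-square test.
- **Adjusted comparison** (Analysis plan): "the estimated relative risk of mortality for heparin vs. placebo will be adjusted by the most important prognostic factors", namely "age, APACHE II score and MOD score at baseline", and this is to be done "using a multiple logistic regression model". The reason given is possible covariate imbalance despite randomisation. Odds ratios are not mentioned, and no conversion to the risk scale is described.
- **Design effect** (Sample size): 80% power for a halving of 28-day mortality with 310 patients, which is a risk-ratio statement.
- **How common death is**: the Sample size section works by "assuming an overall hospital mortality of 25" per cent. The Population section cites a cohort with "an overall hospital mortality of 21" per cent. The Background reports earlier local data: "The overall 28-day sepsis mortality rate ranged from 25% to 40" per cent, depending on blood-culture growth.

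**The concern.** The plan fixes both the quantity (a relative risk) and the estimator (logistic regression), and the two do not match. Exponentiating the treatment coefficient gives an odds ratio conditional on age, APACHE II and MOD score. It approximates a relative risk only when the outcome is rare.

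Two things follow if the text is carried out literally. First, the adjusted effect on mortality would carry the wrong name and look larger than it is on the scale named. Second, it would sit beside an unadjusted relative difference that is on the risk scale. Because adjustment is justified by covariate imbalance, a reader may compare the two figures to judge how much imbalance mattered. That comparison fails even with perfect balance, because the scale has changed and because odds ratios are non-collapsible: conditioning on a prognostic covariate shifts them even when it is balanced.

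**Working it through.** **Inputs.** Risk ratio 0.50 and 155 patients per arm (Sample size). Control mortality of 21% (Population), 25% (Sample size) and 40% (upper end of the range in Background). The 21% and 25% figures are labelled hospital mortality; using them for 28-day mortality is an assumption. Risk ratios of 0.70 and 0.80 are added as illustrations.

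**Step 1: reproduce the plan's figure and confirm its scale.** The control rate behind the 80% mortality power is not stated. Take 25% against 12.5%, a two-sided 0.05 level (sidedness is not stated either) and the normal approximation with pooled variance:

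- mean risk = (0.25 + 0.125)/2 = 0.1875
- z = [0.125 × √155 − 1.96 × √(2 × 0.1875 × 0.8125)] / √(0.25 × 0.75 + 0.125 × 0.875)
- z = (1.556 − 1.082)/0.545 = 0.87, so power is 80.8%

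At the final level of 0.0471 it is 80.1%. Both agree with the stated 80%, so the design effect is a risk ratio at about 25% control mortality.

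**Step 2: express the same effects as odds ratios.** With control risk pc and heparin risk pt = RR × pc, OR = [pt/(1 − pt)] / [pc/(1 − pc)]. For example, at pc = 0.25 and RR 0.50, OR = (0.125/0.875)/(0.25/0.75) = 0.1429/0.3333 = 0.429.

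| Control mortality | RR 0.50 | RR 0.70 | RR 0.80 |
|---|---|---|---|
| 21% | OR 0.441 | OR 0.648 | OR 0.760 |
| 25% | OR 0.429 | OR 0.636 | OR 0.750 |
| 40% | OR 0.375 | OR 0.583 | OR 0.706 |

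Read as a relative risk, the RR 0.50 column would show reductions of 55.9%, 57.1% and 62.5% in place of 50%.

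**Step 3: direction.** The shift is away from 1 on either side. At 25% control mortality, a harmful RR of 1.20 (30% against 25%) gives OR = (0.30/0.70)/(0.25/0.75) = 0.4286/0.3333 = 1.29.

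**Step 4: the effect of conditioning.** Step 2 gives unadjusted odds ratios. The further shift from adjustment depends on how strongly the covariates predict death, which the article does not give. As an illustration only, a simulation of 400,000 subjects assumed one standard-normal covariate with a log-odds slope of 1. For a true RR of 0.50, the adjusted odds ratio was 0.38 at 25% control mortality and 0.31 at 40%. Averaging the predicted risks from the same fitted logistic models over all subjects under each treatment returned an RR of 0.50 in both cases.

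**The case against.** The strongest reply is that the article never says an exponentiated coefficient will be reported as a relative risk. A logistic model can yield a valid adjusted risk ratio by standardisation, as Step 4 shows, and an article may leave that step to a full protocol or analysis plan that is not shown. This stands as a limit: the distortion is conditional on the sentence being carried out literally. It does not clear the sentence, which pairs a measure with a model that does not directly estimate it.

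The consequences are also bounded. This is a supplementary estimate of a secondary outcome, and the risk-scale result is reported in any case through the unadjusted differences.

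Three stronger readings are tempting and not supported:

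- **That the analysis would overstate heparin's benefit.** The shift is away from 1 in both directions, so harm would be magnified too.
- **That mortality of 40% is what the trial expects.** That figure is the upper end of earlier local data and varies with blood-culture growth. The trial's own working figure is 25% hospital mortality, and it deliberately recruits less ill patients as well. The 40% row is an extreme.
- **That the logistic interaction terms would create spurious subgroup effects.** Effect modification depends on scale. A constant RR of 0.70 would be OR 0.68 at 10% risk and 0.54 at 50%, but those risks are assumptions, and nothing in the article favours a constant risk ratio over a constant odds ratio. With about 77 patients per arm in each of two such strata, the log odds ratios would differ by about 0.23 with a standard error of about 0.67, so the trial could hardly detect it. The article already calls these terms hypothesis-generating. At most, it is worth noting that they are on the odds scale.

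**Conclusion.** The point holds as a mismatch between the named measure and the named model. Taken literally, the plan would report a conditional odds ratio under the name of relative risk. At the plan's design effect and its working mortality of 25%, that is 0.43 in place of 0.50, an apparent reduction of 57% against 50%. The gap is slightly smaller at 21% and larger at 40%. For weaker effects it is smaller in absolute terms (RR 0.80 becomes OR 0.75 at 25%). Non-collapsibility adds a further shift of unknown size.

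This rests on two assumptions: that the coefficient is reported without conversion, and that 28-day control mortality is near the figures quoted. The primary outcomes, the chi-square test, the unadjusted differences and the 80% mortality power are untouched. It should be corrected, but it does not threaten the trial's main conclusions.

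**What to change.** Keep the covariates and choose one of the following, stated in the Analysis plan:

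1. Fit the logistic model as planned, average the predicted risks over all randomised patients under heparin and under placebo, and report the adjusted risk ratio and risk difference with delta-method or bootstrap confidence intervals.
2. Estimate the adjusted risk ratio by Poisson regression with robust variance.
3. Keep the logistic coefficient, call it an adjusted odds ratio, and say that it is not to be compared directly with the unadjusted relative difference.

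The first is preferable because it keeps the planned model and puts the adjusted and unadjusted results on the same scale. A short note that the exploratory interactions are on the odds scale would complete it. The cost is a sentence or two of wording and a few lines of code, with no new data, patients or covariates.

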**Results:**

Our primary aims are to estimate the effects of heparin on hospital length of stay and change from baseline Multiple Organ Dysfunction (MOD) score. Secondary objectives are to estimate the effects of heparin on 28-day all-cause mortality, and to estimate the possible effect modification on 28-day all-cause mortality, in subgroups defined by source and site of infection, and baseline values of APACHE II score, MOD score and D-dimer.

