As noted in a recent editorial in JAMA [27], heparin is the most widely available, least expensive, and most frequently used anticoagulant; and despite the common recommendation of continuous infusion of low doses (300–500 units/hour) in the treatment of DIC [13,28], its potential and attractive usefulness as therapy for the treatment of sepsis has not been rigorously tested in a randomized clinical trial. Therefore, we are conducting a clinical trial for testing low dose continuous infusion of unfractioned heparin (500 units/hour for 7 days) as complementary treatment for septic patients.

Our primary aims are to estimate the effects of heparin on hospital length of stay and change from baseline Multiple Organ Dysfunction (MOD) score [29]. Secondary objectives are to estimate the effects of heparin on 28-day all-cause mortality, and to estimate the possible effect modification on 28-day all-cause mortality, in subgroups defined by source and site of infection, and baseline values of APACHE II score, MOD score and D-dimer.

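### The primary length-of-stay test ignores the baseline prognostic factors that the plan adjusts for in secondary mortality, giving up some efficiency on an endpoint with about 51% power

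*Protocol article*

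**What the plan says.** The protocol article (Background) sets two primary endpoints: "Our primary aims are to estimate the effects of heparin on hospital length of stay and change from baseline Multiple Organ Dysfunction (MOD) score". Mortality is secondary: "Secondary objectives are to estimate the effects of heparin on 28-day all-cause mortality".

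For length of stay, Analysis plan gives Kaplan-Meier curves and then fixes the test: "the test statistic for comparison between these two survival distributions will be based on the Log-rank test". It names no strata or covariates. Randomization and following procedures describes 1:1 allocation in permuted blocks of 2, 4 and 6, again without strata.

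Covariates appear later in Analysis plan, in the paragraph on secondary outcomes. That paragraph first observes that random assignment can still leave imbalances that affect treatment estimates. It concludes that the relative risk of mortality will be "adjusted by the most important prognostic factors (age, APACHE II score and MOD score at baseline"), by multiple logistic regression. Nothing similar is said for length of stay.

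Sample size bases the length-of-stay target on "a type I error of 0.05 and a type II error of 0.2", a relative hazard of live discharge of 1.3 and 231 events, reached with 310 patients at 25% hospital mortality. It also says that in-hospital deaths are competing risks and not censored observations.

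**The concern.** The plan gives a reason to adjust, names the covariates and needs them at baseline, yet applies that reasoning only to a secondary estimate. No reason is given for leaving out the primary length-of-stay comparison. The Population section makes enrolment deliberately broad in severity, so baseline severity could plausibly influence time to live discharge. Neither the described randomization nor the described test takes account of it.

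At stake are some power and some protection against chance imbalance on a primary endpoint that has little power to spare. Validity is not at stake: an unadjusted log-rank test in a randomized trial keeps its type I error.

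**Working it through.** **Inputs from the protocol article.** Hazard ratio 1.3, type I error 0.05, type II error 0.2, 231 events, 310 patients and 25% hospital mortality (Sample size); 1:1 allocation (Randomization and following procedures); final significance level 0.0471 (Interim monitoring). Sidedness is not stated; two-sided is taken first.

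**Step 1: the plan's own figure.**
- Freedman: total events = (1.96 + 0.8416)² × (2.3/0.3)² = 7.849 × 58.78 = 461.3, rounded up to 462.
- Schoenfeld: total events = 4 × 7.849 / (ln 1.3)² = 31.40 / 0.06884 = 456.1, rounded up to 457.
- One-sided, the totals are 364 and 360.

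None of these is 231, but 462/2 = 231 exactly. The stated number is what a per-arm count would be if used as the trial total. Also 231/0.75 = 308, in line with the stated 310.

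**Step 2: power of the unadjusted test at 231 events.** z = (√231 / 2) × ln 1.3 = 7.599 × 0.2624 = 1.994. Power = Φ(1.994 − 1.960) = 51.3%. Freedman's form gives 50.9%. At the final level of 0.0471, Schoenfeld gives 50.3%. One-sided at 0.05, it is 63.6%.

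**Step 3: what adjustment could add, taking 1.3 as the hazard ratio of the unadjusted comparison.** The article gives no prognostic strength, so R² is assumed. As an approximation, effective information is multiplied by 1/(1 − R²), so power = Φ(1.994/√(1 − R²) − 1.960).

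| Assumed R² | Power |
|---|---|
| 0 (unadjusted) | 51% |
| 0.05 | 53% |
| 0.10 | 56% |
| 0.20 | 61% |
| 0.30 | 66% |

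Reaching 80% would need R² of about 1 − 231/457 = 0.49.

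**Step 4: a second reading, taking 1.3 as the hazard ratio conditional on the covariates.** Cox simulation: 310 patients, exponential times, each exit a live discharge with probability 0.745 (about 231 events), one normal prognostic covariate, 1,000 runs per row. The covariate's log-hazard SD is assumed.

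| Assumed SD | Unadjusted | Adjusted |
|---|---|---|
| 0.3 | 42.5% | 49.3% |
| 0.5 | 38.3% | 51.3% |
| 0.8 | 28.8% | 50.2% |
| 1.0 | 23.7% | 51.4% |

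The Monte Carlo standard error is at most √(0.25/1000) = 1.6 percentage points. Adjustment helps in every row, but power stays near 50% because the event count is unchanged.

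**The case against.** **The unadjusted test is valid, and mortality gets no stronger test.** Both parts stand. The secondary mortality hypothesis is itself tested by an unadjusted chi-square; the logistic model supplies an additional adjusted estimate. It would therefore be wrong to say that the plan gives mortality a better main test than length of stay. What remains is that the plan's imbalance argument leads to an adjusted estimate for mortality and to none for length of stay.

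**The gain is assumed.** This stands. The plan calls the three factors prognostic when discussing mortality, and nothing in the article quantifies their relation to time to live discharge.

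**Adjustment has a price.** This stands in part. A regression hazard ratio is conditional on the covariates rather than marginal, and the model adds assumptions. The first interim analysis has also taken place, with results by arm going to the monitoring board, so who makes the change matters.

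**A reader might infer that the MOD endpoint has the same fault and is also short of power.** The article does not support this. The sentence saying that the analysis must "model both the regression of *Y *(the outcome measure) on *x *(the intervention") describes a class of model and does not list covariates, which a condensed article may leave to fuller documents. Table 3 states 97% to 100% power and gives no standard deviation, so no shortfall can be shown. Moving baseline MOD from the response into the covariates could even cost precision on a rate of change, because the slope loses its first time point. For assumed visits 0 to 3, the sum of squared time deviations falls from 5 to 2 (slope variance up 2.5-fold). For visits 0 to 7 it falls from 42 to 28 (1.5-fold).

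**A reader might also infer that missing adjustment explains the 51%.** It does not; Step 1 of the working points to the event count.

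**Conclusion.** The point holds for length of stay only, and as a matter of efficiency and consistency. The plan fixes an unadjusted primary test while its own argument for adjustment applies to that endpoint too. At 231 events, a hazard ratio of 1.3 and two-sided 0.05, power is about 51%. For an assumed R² of 0.05 to 0.30, adjustment would raise it to about 53% to 66%, a gain of some 2 to 15 percentage points. If 1.3 is instead the conditional hazard ratio, adjustment prevents a loss of roughly 7 to 28 points over the assumed range but leaves power near 50%.

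On neither reading does adjustment restore 80% within the ranges tried. The event-count error is separate and larger, and should be corrected on its own account. The change is worth making because it is cheap, but the trial's validity does not depend on it.

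**What to change.** Before unblinding, pre-specify as the primary length-of-stay analysis a comparison of discharge alive adjusted for age, APACHE II and baseline MOD. Either of two forms would serve:
- a covariate-adjusted hazard regression, stating whether the hazard is cause-specific or subdistribution; or
- a stratified log-rank test, with cut points for the strata set in advance.

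Handle in-hospital death as the competing event, as Sample size already says. Keep the unadjusted log-rank test as a supporting analysis. Leave the MOD model out of this change.

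The decision should be made and dated by people blinded to interim results by arm. That excludes the data-coordinating-center statistician who holds the blind, and the monitoring board. The amendment should also say whether any remaining interim look at length of stay uses the adjusted analysis.

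The cost is an amendment to the analysis wording. It needs no further patients or measurements, since the mortality model already requires the covariates. The small downsides are a conditional rather than marginal hazard ratio and one more modelling assumption.
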